### **2.4.3 Physiological and Processes of care outcomes**

- Vital signs such as mean arterial pressure (MAP), heart rate (HR), respiratory rate (RR), diuresis and systemic body temperature and fluid balance will be recorded daily from inclusion until ICU discharge (censored day 28);
- Routine laboratory test parameters for organ function assessment: haemoglobin, platelets count, white blood cells count, troponin, coagulative parameters (INR, PT, aPTT), parameters for liver (AST, ALT, bilirubin) and renal function (creatinine) will be recorded daily from inclusion to ICU discharge (censored at day 28);
- Blood cells count, C-reactive protein (CRP), procalcitonin (PCT) and interleukin 6 (IL-6) will be recorded daily from inclusion to ICU discharge (censored at day 28);
- Ventilation mode, inspired oxygen fraction and arterial blood gas analysis parameters will be recorded daily from inclusion to ICU discharge from (censored at day 28);
- Adjunctive treatment such as pronation cycles, Nitric Oxide or ECMO will be recorded daily from inclusion to ICU discharge from (censored at day 28);
- New blood, respiratory and urinary-tract infections will be recorded from randomization to day 28;
- Viral reactivation measured by CMV DNA titres will be recorded from randomization to day 28;
- Need of new renal replacement therapy (intermittent haemodialysis or continuous veno-venous hemofiltration) from randomization to 28 days.

### **2.5 PARTICIPANT TIMELINE**

See APPENDIX 4 for a timeline-scheme of the trial.

### **2.6 SAMPLE SIZE**

The target sample size is based on the hypothesis that the combined use of UHF and steroids versus the LMWH group will significantly reduce the risk of 28-day death. The overall sample size in this study is expected to be 210 with a randomization 1:1:1. Assuming an alpha of 2.5% (two tailed) and mortality rate in LMWH group of 50%, as indicated from initial studies of ICU patients, the study will have an 80% power to detect at least a 25 % absolute reduction in the risk of death between:

a) LMHW + steroids group and LMWH group

or

b) UHF + steroids group and LMWH group

The study has not been sized to assess the difference between LMHW + steroids group and UHF + steroids group, therefore the results obtained from this comparison will need to be interpreted with caution and will need further adequately sized studies to be confirmed.

### **2.7 RECRUITMENT**

All centres participating in this study are experienced in investigator-initiated studies. On the basis of a conservative estimation, that 8 participating sites admit an average of 3 eligible patients per month per centre (24 patients/month). Assuming that 80 % of eligible patients are enrolled, recruitment of 210 participants will be completed in around 10 months. Every month, recruitment status will be evaluated, and a newsletter will be disseminated, including any practical, clinical or scientific issue arisen.

### **3.0 METHODS: ASSIGNEMENT OF INTERVENTIONS**

#### **3.1 Allocation and blinding**

A block randomisation will be used with variable block sizes (block size 4-6-8), stratified by 3 factors: Centre, BMI (<30; ≥30) and Age (<75 e ≥75). Central randomisation will be performed using a secure, web-based, randomisation system. The allocation sequence will be generated by the study statistician using computer generated random numbers. The attending physician, according to the protocol and the randomization, will note the inclusion of the patient in the study. Clinicians will receive all the instructions to attend the protocol and paper printed instructions will be distributed in the participating centres. The local coordinator will be responsible of the training and information of the personnel about the study protocol. The study is conceived as open-label: the patients and all the healthcare personnel will be aware of the group allocation.

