### **1.3 TRIAL DESIGN**

The study is designed as a multicenter, national, interventional, randomized, investigator sponsored, three arms study. Patients, who satisfy all inclusion criteria and no exclusion criteria, will be randomly assigned to one of the three treatment groups in a ratio 1:1:1.

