## **2.0 METHODS: PARTICIPANTS, INTERVENTIONS AND OUTCOMES**

### **2.1 STUDY SETTING**

The study will involve 8 Italian Academic and non-Academic Intensive Care Units.

See list of centres in APPENDIX 1.

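### Block sizes 4 and 8 cannot be balanced across three arms, so the stated block list conflicts with the 1:1:1 design

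*Protocol*

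**What the plan says.** Three places in the protocol bear on this.

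- Section 1.3 (Trial design): eligible patients "will be randomly assigned to one of the three treatment groups in a ratio 1:1:1".
- Section 2.6 (Sample size): "The overall sample size in this study is expected to be 210 with a randomization 1:1:1", which is 70 per arm.
- Section 3.1 (Allocation and blinding): "A block randomisation will be used with variable block sizes (block size 4-6-8), stratified by 3 factors". The factors are centre, BMI (two levels) and age (two levels).

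No other section gives different block sizes. None says how a block that three arms do not divide evenly is to be filled. Section 3.1 also says that the trial is open-label and that randomisation runs through a central web-based system.

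**The concern.** Permuted blocks are used so that each completed block reproduces the allocation ratio. With three arms at 1:1:1 this requires a block length divisible by three. The lengths 4, 6 and 8 are all even and would suit a two-arm 1:1 trial; for three arms, two of the three do not work.

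The procedure therefore cannot be carried out as written without a decision that the protocol does not record. Whoever builds the list must depart from the stated sizes, invent a rule for the surplus places, or accept whatever the software does. These choices lead to different arm sizes, and a reader of the protocol cannot tell which was made. What is at stake is the planned 70 per arm, and balance by centre, BMI and age. Section 4.2.1 says that the main analyses will not account for the stratification factors, so any imbalance on them would stay unadjusted there.

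**Working it through.** **Inputs from the protocol**

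- Three arms, 1:1:1 (sections 1.3 and 2.6).
- Block sizes 4, 6 and 8 (section 3.1).
- Strata: "stratified by 3 factors: Centre, BMI (<30; ≥30) and Age (<75 e ≥75"), with eight centres (section 2.1: "The study will involve 8 Italian Academic and non-Academic Intensive Care Units"). That is 8 × 2 × 2 = 32 strata, or 210 / 32 = 6.6 patients per stratum on average.
- Two-sided alpha 0.025, control mortality 50%, 25-point absolute reduction (so 50% v 25%), power 80%, N = 210 (section 2.6).

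**Step 1. Reproduce the planned sample size.** Two proportions, pooled variance under the null, no continuity correction:

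n = [z(0.9875) × √(2 × 0.375 × 0.625) + z(0.80) × √(0.50 × 0.50 + 0.25 × 0.75)]² / 0.25²

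With z(0.9875) = 2.2414 and z(0.80) = 0.8416, n = 69.97, so 70 per arm and 3 × 70 = 210. The stated figure reproduces under equal arms. The normal-approximation power at 70 v 70 is 80.0%. Exact binomial power of the pooled chi-square test is 80.7%, and this is the reference value in step 4.

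**Step 2. Divisibility.**

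| Block size | Remainder after division by 3 | Best possible split |
|---|---|---|
| 4 | 1 | 2:1:1 |
| 6 | 0 | 2:2:2 |
| 8 | 2 | 3:3:2 |

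Only the block of 6 can be balanced.

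**Step 3. Effect on arm sizes.** The protocol states no surplus rule, so two were tried. Each scenario was simulated 3,000 times with 210 patients spread at random over 32 equally likely strata and block sizes drawn with equal probability. Equal strata are an assumption; the documents do not give the stratum sizes. The gap is the largest arm minus the smallest.

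| Block sizes | Surplus rule (assumed) | Mean arm sizes | Mean gap | 95th percentile of gap |
|---|---|---|---|---|
| 4, 6, 8 | Drawn at random | 70/70/70 | about 7.5 | about 14 to 15 |
| 4, 6, 8 | Always the same arms (2:1:1 and 3:3:2 in fixed order) | 82.7/68.8/58.5 | about 24 | 34 |
| 3, 6 | None needed | 70/70/70 | about 5.5 | 11 |

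**Step 4. Power under the fixed-surplus rule.** Exact pooled chi-square power, alpha 0.025 two-sided, 50% in the LMWH arm against 25% in a steroid arm. Arm sizes are rounded to 83, 69 and 59. Both planned comparisons share the LMWH control, so the result depends on which size falls to LMWH.

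| LMWH arm is | Comparisons (LMWH v steroid arm) | Power |
|---|---|---|
| Largest (83) | 83 v 69; 83 v 59 | 83.3%; 79.8% |
| Middle (69) | 69 v 83; 69 v 59 | 83.1%; 76.4% |
| Smallest (59) | 59 v 83; 59 v 69 | 80.1%; 76.4% |

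Against 80.7% at 70 v 70, one comparison may gain up to about 2.6 points (83.3 − 80.7) and another may lose up to about 4.3 points (80.7 − 76.4).

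**The case against.** The strongest reply is that a block need not be balanced for the trial to be 1:1:1. If the surplus places are assigned at random, every patient still has probability one third for each arm, expected sizes are 70/70/70, and the randomised comparison is valid. That is correct. A reader might infer from the block list that the trial cannot achieve 1:1:1 at all, or that the web system would reject the list. The documents support neither reading: the first fails under random surplus, and the second is speculation, because the protocol does not describe how the system behaves.

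A second reply is that much of the arm-size spread comes from unfinished blocks in 32 small strata and would remain after the correction. This also stands: the 95th percentile of the gap is still 11 with blocks of 3 and 6.

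Third, the 83/69/59 split rests on a surplus rule that the protocol does not state, and no single power figure describes it. If LMWH, which is Group 1, were the largest arm, one comparison would gain power and the other would lose about one point. A reader might infer a general loss of power from the block sizes, and the calculation does not show one.

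These replies limit the consequences. They do not remove the contradiction: two of the three stated block sizes cannot be balanced for three arms, and the protocol supplies nothing to resolve it. Nor is this a detail left to the statistical analysis plan, since the protocol itself fixes the sizes.

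**Conclusion.** The point holds as an internal inconsistency between section 3.1 and sections 1.3 and 2.6. That part is plain arithmetic and needs no assumption.

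The size of the effect does rest on assumptions. With random surplus it is modest: somewhat wider variation in arm sizes, with the ratio intact in expectation. With a fixed surplus it is larger, with mean arm sizes well away from 70 and power for one planned comparison as low as about 76% if LMWH is the middle or smallest arm. Both results assume 32 equally likely strata and equal use of the three block sizes.

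Unequal arms do not in themselves bias the comparison, and the total of 210 stands. Should-fix: a stated design parameter is wrong as written and is easily corrected, but the documents do not show that the trial's validity is at risk.

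**What to change.** In section 3.1, replace block sizes 4-6-8 with randomly varied sizes that are all multiples of three, for example 3 and 6. Sizes of 3, 6 and 9 would also be consistent with the design, but at about 6.6 patients per stratum the longer blocks would often stay incomplete.

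Check the list actually programmed in the web system against the corrected text. If anyone has been randomised from a 4-6-8 list, document the surplus rule that was used and the realised allocation.

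The cost is a one-line amendment and, where needed, a regenerated list; the number of arms, alpha and N do not change. The small downside is that blocks of 3 are somewhat easier to predict in an open-label trial stratified by centre. Random mixing with the longer size limits this, as does keeping the block sizes out of the protocol that section 5.3 has distributed to every centre.

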### **5.3 Auditing**

The principal investigator and the SC will provide all the necessary information and material to the participating centres in order to standardize all the protocol-related procedures and to avoid unexpected variability between centres. A preliminary audit between the coordinating centre and the satellite centres will be performed before to start the recruitment phase to offer the major consensus and homogeneity possible. Printed and electronic informative material (complete original protocol, informed consent modules, informative modules for patients and relatives, recruitment check-list, graphic timeline of interventions and visits, order-list for physicians and nurses) will be distributed to every centre.

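### Block sizes 4-6-8 are printed in the protocol sent to every centre of an open-label three-arm trial: a small avoidable gain in predictability, and a larger one if only blocks of 6 are workable

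*Protocol*

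**What the plan says.** Protocol Section 3.1 (Allocation and blinding) fixes the scheme: "A block randomisation will be used with variable block sizes (block size 4-6-8), stratified by 3 factors: Centre", followed by "BMI (<30; ≥30) and Age (<75 e ≥75". With the 8 centres of Section 2.1 this makes 8 × 2 × 2 = 32 strata, four in each centre. Section 1.3 sets three arms at 1:1:1.

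Allocation is central: "Central randomisation will be performed using a secure, web-based, randomisation system". It is also open: "the patients and all the healthcare personnel will be aware of the group allocation". Inclusion is recorded locally: "The attending physician, according to the protocol and the randomization, will note the inclusion of the patient in the study".

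Section 5.3 (Auditing) lists what the sites receive: "Printed and electronic informative material (complete original protocol" is among the items, and the set "will be distributed to every centre".

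**The concern.** A central web system conceals the list. It does not stop someone working out the likely next entry from entries already seen. Here the strata lie within centre, past allocations are visible, blocks are small, and the set of sizes is in the hands of those who decide on enrolment.

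If staff can form a view of the next arm, they can let it influence whom they enrol. Two exclusion criteria in Section 2.2.2 rest on judgement (high bleeding risk, and too sick to benefit). Both relate to prognosis, and the first relates directly to full-dose heparin. Selection on unmeasured prognosis would bias 28-day mortality with only 70 patients per arm, and no analysis reliably removes it.

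The same sentence has a second weakness that determines how serious the first is. A block of 4 or 8 cannot hold equal numbers of three arms, and the protocol gives no rule for filling one.

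**Working it through.** **Inputs.** From the protocol: 210 patients (2.6), 8 centres (2.1), three arms 1:1:1 (1.3), block sizes and strata (3.1), 3 eligible patients per centre per month with 80% enrolled (2.7), invasive ventilation for under 96 hours (2.2.1).

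**The plan's own figure.** The protocol gives no figure for predictability. The total that sets stratum size reproduces. For 50% against 25%, two-sided alpha 0.025 and 80% power, n per arm = [2.2414 × √(2 × 0.375 × 0.625) + 0.8416 × √(0.25 + 0.1875)]² / 0.25² = 69.97, so 70 per arm and 210 in all. That is 210/8 = 26.25 per centre and 210/32 = 6.56 per stratum.

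**Assumptions not in the protocol.** The three block sizes are equally likely. Fill rule A (near-balanced): 4 = one of each arm plus one random arm, and 8 = 3+3+2 in random order. Fill rule B: 4 = one of each and 8 = two of each, with every leftover place drawn at random. Rule C: only blocks of 6 are used. The uneven split takes 65% with BMI under 30 and 88% aged under 75, with 26 patients per centre.

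**Method.** Allocation sequences were simulated (15,000 strata; 4,000 for the 26-patient case). Before each patient, the exact probability of each arm was computed for someone who knows the sizes and the stratum's history. The comparator does not know the sizes and names the arm least used so far. Chance is 33.3%.

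| Blocks | Patients in stratum | Best guess, sizes known | Least-used arm, sizes unknown | Next arm certain (sizes known) |
|---|---|---|---|---|
| 4/6/8, rule A | 7 | 48.1% | 47.9% | 0.2% |
| 4/6/8, rule A | uneven split | 47.7% | 46.7% | 0.4% |
| 4/6/8, rule A | 26 | 49.9% | 46.7% | 0.4% |
| 4/6/8, rule B | 7 | 47.6% | 47.4% | 0.3% |
| 4/6/8, rule B | 26 | 49.1% | 45.8% | 0.6% |
| 6 only, rule C | 7 | 52.8% | 52.9% | 17.1% |
| 6 only, rule C | uneven split | 51.6% | 51.6% | 14.1% |
| 6 only, rule C | 26 | 54.6% | 54.6% | 18.5% |

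Under rule A, with 7 or 26 patients, one arm has probability of at least 50% for 41–42% of patients and one arm falls below 10% for 16–18%. An arm can be excluded outright for about 3% under rule A and 40–43% under rule C.

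**What disclosure adds under 4/6/8.** Rule A: 48.1 − 47.9 = 0.2 points with 7 patients, 47.7 − 46.7 = 1.0 with the uneven split, and 49.9 − 46.7 = 3.2 with 26. The 26-patient case is an upper bound, because it puts a whole centre's mean accrual into one of its four strata.

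**Certainty under rule C, by hand.** A block of 6 has 6!/(2!2!2!) = 90 orders. The sixth place is always known. The fifth is known when the last two places are the same arm: 3 × 4!/(2!2!) = 18 orders, or 18/90 = 0.2. So 1.2 places per full block are certain: 1.2/7 = 17.1% over 7 patients and 4 × 1.2/26 = 18.5% over 26. This agrees with the simulation.

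**Could staff wait for a preferred arm?** Accrual is 3 × 0.8 = 2.4 per centre per month, or 2.4/4 = 0.6 per stratum per month: about one patient every 50 days (30/0.6). Even if a whole centre fell in one stratum it would be one every 12.5 days (30/2.4). The window is 96 hours, or 4 days.

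**The case against.** The strongest reply is that printing the sizes hardly matters. In a stratum of average size the guess rate is 48% with or without them. The scheme already has varying sizes, central web allocation and a statistician-generated list. Section 4.1 says every patient who meets the inclusion criteria will be randomised and has a monitor check eligibility. Hiding the sizes leaves about 47–48% guessable, and the change needs ethics committee authorisation.

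Most of this stands. The average guess rate comes from small blocks in an open-label trial, and disclosure accounts for little of it. Deferring a patient until a preferred arm comes up is largely impracticable on the protocol's own accrual figures. What does not fall is the possibility of declining to enrol on a judgement criterion, and the fact that known sizes let staff recognise the moments when an arm is nearly or wholly ruled out. The safeguards also do not settle whether sizes 4 and 8 can be used at all. If they cannot, the varying sizes become one fixed size.

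A reader might infer from the printed sizes that physicians can simply foresee the next arm. The protocol does not support that. With varying sizes and a separate sequence for each centre, BMI and age stratum, the best guess is wrong about half the time and certainty is under 1% with either fill rule for 4/6/8. Nor does anything in the protocol suggest that allocations would be misused.

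**Conclusion.** The point holds as a modest, preventable weakness. Enrolling staff can guess the next arm about 48–50% of the time against 33% by chance. Disclosure contributes about 0–3 points of that, and nearer 0–1 at realistic stratum sizes. Certainty is below 1% if 4/6/8 blocks are filled as evenly as possible. It rises to about 14–18% if only blocks of 6 are workable and staff realise it (17–18% at average stratum size).

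These figures rest on equally likely block sizes, on the assumed fill rules and on the assumed stratum sizes, none of which the protocol states. The premises themselves are in the text: the sizes are printed, the protocol goes to every centre, allocations are visible, and 4 and 8 are not divisible by three.

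**What to change.** In Section 3.1, replace the list of sizes with wording such as: permuted blocks of varying size, details held in a restricted randomisation document. Because 4-6-8 has already been disclosed, have the statistician issue a new list for patients not yet randomised, with undisclosed varying sizes that are multiples of 3 and preferably not very small.

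Multiples of 3 are needed so that each complete block delivers 1:1:1. They do not by themselves make guessing much harder. Sizes 6/9/12, for example, give a best guess of 46% over 7 patients, 48% with the uneven split and 51% over 26, with certainty of 0–2% even if disclosed. Withholding the sizes means staff cannot know when an arm is certain or excluded.

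The cost is a reworded sentence, a regenerated list and a protocol amendment, which Section 6.1 allows to be applied only after written ethics committee authorisation. No extra patients and no site procedures are involved. The gain in average unpredictability is small. The main benefits are blocks that fit three arms and removal of the near-fixed-block risk.

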### **4.0 METHODS: DATA COLLECTION, MANAGEMENT AND ANALYSIS**

#### **4.1 Data collection and management**

Every patient who meets the inclusion criteria will be included and randomised in the three groups. The study data will be collected along the entire study period in a dedicated electronic Case Report Form (eCRF). The eCRF will be provided by the steering committee with proper options to minimize data entry errors: the datasheet will incorporate un-amendable fixed intervals of values (for continuous variables) and pre-defined coding system (for binary or categorical variables). Data entry will be performed and double-checked from a dedicated researcher in each centre; in order to limit collection errors, 10% of all records will be randomly re- checked from the PI in each participating centre. The data collection will be also checked by a Clinical Monitor, by phone calls as agreed with the investigators. The study Monitor will be responsible for performing the monitoring in accordance with good clinical practice (GCP) guidelines. The investigators will agree on monitoring phone calls to assess the progress of the study, verify adherence to the protocol, check the eligibility of patients, the accuracy and completeness of the eCRF, check the correlation between the data reported into eCRF and those recorded in the hospital documents (medical records, patient registries, etc.), check for the correct reporting of adverse events, verify that evaluations planned and documentation of the study are properly stored and handled. Data will be collected and stored in on hardware supports in every participant centre and sent to the coordinating centre at the end of the study and protected by password to prevent unintentional modifications or deletion. Each satellite centre will monthly communicate and report via e-mail with the coordinating centre about number of recruited patients, eventual missing data or missing visit or any kind of problem correlated to data collection. Data related to the study will be stored for eventual further analysis or study purpose for 10 years after the end of the study. All the data about the included patients will be extrapolated from the clinical documentation and recorded in an eCRF from adequately trained researcher. Demographic information (gender, age) and co-morbidities, will be registered at the inclusion, severity of critical illness (quantified by the Simplified Acute Physiology Score II,

SAPS II) will be calculated by the data from the first 24 h of ICU stay. During the study duration clinical and laboratory parameters will be evaluated and recorded following the timeline schedule in APPENDIX 4: SOFA score and its components, vital signs such as mean arterial pressure (MAP), heart rate (HR), respiratory rate (RR), systemic temperature, diuresis, fluid balance, data from routine laboratory test such as haemoglobin, platelets count, white blood cells count, troponin, coagulative parameters (INR, PT, aPTT), parameters for liver and renal function (AST, ALT, bilirubin, creatinine), oxygen inspired fraction, blood gas analysis results (BGA), ventilation mode, need of adjunctive therapy for ARDS (i.e. prone position, Nitric oxide, ECMO), blood cells count, C-reactive protein (PCR), procalcitonin (PCT), interleukin-6 (IL-6), immunoglobulin titers (IgG, IgM, IgA), occurrence of ICU-acquired (from 48 hours after ICU admission) blood, respiratory and urinary-tract infection and the implicated microorganisms, reactivation of viral infections (CMV-DNA titres). Other recorded parameters will include duration and mode of ventilatory support in days, duration and type of antiviral, antibiotic and antifungal therapy in days, need of vasoactive drugs, use of immune-modulatory drugs or other adjunctive treatment for COVID-19 pneumonia.

As a blood-bank for possible further biochemical investigations (e.g. cytokines titers, different biomarkers), for each patient who will be included in the study a blood sample of about 6 ml will be collected at baseline, day 7 and 28 or at ICU discharge and stored, after centrifugation, at -70°C in the local laboratory of each site.

